### Sample size calculation

This study is a superiority trial. The sample size was calculated on the basis of 6MWD by using PASS software (version 15.0). Based on the previous clinical studies of TCEs and acupuncture intervention for COPD (19, 40, 41), the added values of 6MWD after the intervention of TCEs, acupuncture, and exercise-combined therapy were estimated to be 34.5, 32, and 38, respectively, with the assumption that the mean value of 6MWD in the control group was 297.9 and the standard deviation was 37.4. By setting alpha to 0.0083 (two-sided) and the power to 0.80, a minimum sample size of 26 participants per group was calculated. Considering a 20% attrition rate, a total of 132 participants with 33 participants per group is a reasonable sample size for this study.

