### Statistical analysis

An independent statistician who is not involved in outcome measurement will perform statistical analysis using SPSS software (version 24.0). All participants will be included in the intention-to-treat analyses. The multiple imputation method will be utilized to analyze missing data. Continuous data will be expressed as mean ± SD or median ± quartile interval, and enumeration data will be expressed as a relative ratio. Comparisons of baseline differences between groups will be performed using ANOVA or the Kruskal–Wallis H test for continuous variables and χ2 for categorical variables. Comparisons within each group (before and after 8 weeks of intervention) will be evaluated using a paired t-test or non-parametric test. Comparisons of endpoint differences between groups will be assessed using a 2 × 2 ANOVA (group × time) or the Kruskal–Wallis H test, with analysis of covariance applied when baseline is not uniform. In addition, a Difference-in-Difference (DID) analysis will be conducted to further assess the intervention effects while accounting for baseline differences and time trends.Multiple comparisons between the intervention arms will be performed using SNK-q test or the Nemenyi test. A *p* value of <0.05 will be considered statistically significant.

To further evaluate the discriminatory ability of each intervention in improving exercise tolerance, the area under the receiver operating characteristic curve (AUC) will be calculated for each intervention group, using the improvement in 6MWD as the classification criterion. Treatment effectiveness will be defined as an improvement in 6MWD ≥ 54 meters (minimal clinically important difference) (55). AUCs will be compared using the DeLong test with MedCalc software (MedCalc Software Ltd., Ostend, Belgium). A *p* value of <0.05 will be considered statistically significant.

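### 6MWD is sized at a two-sided alpha of 0.0083 but analysed with Student-Newman-Keuls at 0.05, which over four arms can let the family-wise error reach almost 10%

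*Protocol article*

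**What the plan says.** The Sample size calculation section bases the trial on 6MWD: "By setting alpha to 0.0083 (two-sided) and the power to 0.80". The assumed gains over control for Qigong, acupuncture and the combination "were estimated to be 34.5, 32, and 38, respectively" metres, and "the mean value of 6MWD in the control group was 297.9 and the standard deviation was 37.4". The result is 26 per group, raised to 33 per group (132 in total) for 20% attrition. The section does not explain the value 0.0083.

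The Statistical analysis section compares endpoints by ANOVA or Kruskal-Wallis, with ANCOVA if baseline is uneven and a difference-in-difference analysis in addition. It then says: "Multiple comparisons between the intervention arms will be performed using SNK-q test or the Nemenyi test". The threshold that follows is a p "value of <0.05 will be considered statistically significant". The value 0.0083 does not appear there, and no other family-wise rule is given for the primary outcome.

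**The concern.** The two sections give different decision rules for the same primary outcome. Planning uses a level that protects a family of six pairs. The analysis uses a step-down range test at 0.05, and with four groups that test protects the family only in some configurations of the true means.

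At stake is which 6MWD claims may be made. The Introduction hypothesises that each active regimen works and that the combination beats the single interventions. The Abstract presents the trial as evidence for acupuncture as an adjuvant. If acupuncture does nothing, alone or on top of Qigong, the means form two equal pairs: control with acupuncture, and Qigong with the combination. This is the pattern in which SNK over four arms is weakest, and the false claims that it would then allow are claims about acupuncture.

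**Working it through.** **Inputs** (all from Sample size calculation): alpha 0.0083 two-sided, power 0.80, SD 37.4, gains 34.5, 32 and 38 m, 26 per group before attrition and 33 after.

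**1. The plan's own figure.** The normal approximation for 38 m is n = 2 × [(2.64 + 0.84) × 37.4/38]² ≈ 23.5, so 24 per group. The exact t-test needs 26 (power 0.815). A four-group ANOVA at 0.0083 with means 0, 34.5, 32 and 38 also needs 26 (power 0.810). Then 26/0.8 = 32.5, so 33, and 4 × 33 = 132. The stated size is reproduced at 0.0083.

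**2. Where 0.0083 comes from.** Four arms give 4 × 3/2 = 6 pairs, and 0.05/6 = 0.00833. The match is exact to the digits given, but the six-pair origin is an inference.

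**3. The hurdles.** With 26 per arm, the pooled error has 100 degrees of freedom and the standard error of a difference is 37.4 × √(2/26) = 10.37 m.

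| Rule | Critical t | Smallest significant difference |
|---|---|---|
| SNK, adjacent means | 1.98 | 20.5 m |
| SNK, range of three | 2.38 | 24.7 m |
| Tukey (and SNK, range of four) | 2.61 | 27.1 m |
| Bonferroni, 0.0083 | 2.69 | 27.9 m |

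SNK reaches the adjacent-pair hurdle only after every wider range containing that pair has been rejected.

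**4. Theoretical limit.** When two equal pairs are far enough apart, the wider ranges are almost always rejected. Two true null hypotheses are then each tested at 5%: 1 − 0.95² = 9.75%.

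**5. Simulated family-wise error** (SD 37.4, 200,000 trials per cell):

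| True means (control, acupuncture, Qigong, combination) | SNK, n=26 | SNK, n=33 | Tukey | Bonferroni 0.0083 |
|---|---|---|---|---|
| all equal | 5.0% | 5.1% | 5.0–5.1% | 4.1–4.2% |
| 0, 34.5, 34.5, 34.5 | 5.0% | 5.0% | 2.8% | 2.3% |
| 0, 0, 32, 32 | 9.5% | 9.6% | 2.0% | 1.6% |
| 0, 0, 34.5, 34.5 | 9.7% | 9.7% | 2.0% | 1.6% |
| 0, 0, 38, 38 | 9.8% | 9.7% | 2.1% | 1.7% |

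Simulation error is about 0.07 percentage points near 9.7%. Requiring a significant ANOVA first leaves the last three rows unchanged and lowers the SNK figures in the first row to 4.2–4.3%. At 34.5 m and 26 per arm, unprotected t-tests on the two null pairs give 9.8% against 9.7% for SNK, so the step-down gate removes almost nothing there.

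**6. SNK on three arms only.** The simulated error is 4.9% to 5.0%. On this reading the three comparisons with control have no stated rule beyond 0.05. Their joint error is bounded only by 3 × 0.05 = 15%, which is a ceiling and not an estimate.

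**The case against.** The strongest reply concerns scope. The sentence on multiple comparisons refers to the intervention arms, and Study design uses similar words for the three active groups as distinct from control. Read that way, SNK holds 5%, and the two-pair case cannot arise because control is outside the family. This stands as a reading. It does not remove the conflict: the comparisons with control, whose effects the sample size was built on, then have no multiplicity rule, although they were planned at 0.0083.

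A second reply is that almost 10% is a worst case. That also stands. The plan's own assumed gains lie close to three similar arms and one lower, where SNK gives 5%. The two-pair case contradicts the assumed 32 m gain for acupuncture. But error control is wanted precisely when the hoped-for effect is absent.

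A reader might infer more than the documents support:

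- **Nemenyi fails too.** The figures above are for SNK, and no family-wise failure of Nemenyi has been shown.
- **Multiple imputation has nothing to pool.** The plan states "The multiple imputation method will be utilized to analyze missing data", and its ANCOVA and difference-in-difference analyses yield estimates with standard errors that can be pooled.
- **The sample size is wrong.** Sizing at a stricter level than the analysis uses is conservative for power.
- **SNK amounts to unprotected t-tests, or doubles a stated error rate.** SNK tests adjacent pairs only after wider ranges reject, and the plan states a significance threshold without naming a family-wise rate.

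**Conclusion.** The point holds in a limited form. The planned level of 0.0083 and the analysis rule of SNK at 0.05 are inconsistent, and this does not depend on how the ambiguous sentence is read.

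If SNK covers four arms, its family-wise error is about 5% under the complete null or with one arm different. It rises to about 9.5% to 9.8% with two equal pairs 32 to 38 m apart. These figures assume normal outcomes, a common SD of 37.4 and equal arms of 26 or 33. If SNK covers only the active arms, the gap is the unadjusted comparisons with control. It would be wrong to say that the trial runs a 10% error in general. It should be settled before analysis, because it decides which primary-outcome differences count as significant.

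**What to change.** For 6MWD, replace SNK with pairwise contrasts from one model containing all four arms. Adjust the six contrasts by Tukey or Holm, or test each at p<0.0083, and report adjusted confidence intervals. State that 0.05 is the family-wise level, state that control belongs to the family, and give the same rule in Sample size calculation and Statistical analysis, with the reason for 0.0083. This works under either reading of the present sentence.

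The cost is wording, with no added participants. Some differences that SNK would call significant will no longer be: the hurdle for adjacent means rises from 1.98 to about 2.61 (Tukey, 26 per arm). Against the planned alpha nothing is lost, since Tukey's critical t is 2.61 against 2.69 at 26 per arm and 2.60 against 2.68 at 33. With 33 per arm, power for one pair at 38, 34.5 and 32 m is 0.93, 0.87 and 0.81 with Tukey, and 0.92, 0.85 and 0.78 at 0.0083. With 26 it is 0.85, 0.76 and 0.68 against 0.83, 0.74 and 0.65.

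### The supplementary ROC analysis names 6MWD improvement both as classifier and, cut at 54 m, as the state to be classified; read literally it cannot compare the interventions

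*Protocol article*

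**What the plan says.** The second paragraph of the Statistical analysis section gives its purpose as follows: "To further evaluate the discriminatory ability of each intervention in improving exercise tolerance". It then specifies four things:

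- **Unit:** "the area under the receiver operating characteristic curve (AUC) will be calculated for each intervention group".
- **Variable:** "using the improvement in 6MWD as the classification criterion".
- **Responder definition:** "Treatment effectiveness will be defined as an improvement in 6MWD" of at least 54 m, described as the minimal clinically important difference.
- **Test:** "AUCs will be compared using the DeLong test with MedCalc software", with significance at p < 0.05.

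No score, baseline predictor or other marker is named for the curve. The Study design section counts three intervention groups (PQG, AG, PAG), so no AUC is planned for CG.

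**The concern.** An ROC curve needs two separate things: a marker, and a state that the marker is meant to detect. Here one variable, the 6MWD gain, appears to supply both. If so, the AUC is fixed before any data are collected and says nothing about treatment.

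The AUC also measures how well a marker separates two states. It does not measure how well a treatment works, and inside a single arm there is no control group to separate from.

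This paragraph is the only place where the protocol ties its primary outcome to a clinically important difference. The trial's hypothesis is that the combination does better than either single intervention. An analysis that cannot tell the arms apart wastes the one planned look at responders.

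**Working it through.** **Inputs**

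- Unit, variable, responder cut-off and test: Statistical analysis section, as quoted above.
- Assumed 6MWD gains: Sample size calculation section, where the values for traditional Chinese exercise (PQG), acupuncture (AG) and combined therapy (PAG) "were estimated to be 34.5, 32, and 38, respectively".
- Spread: the same section states that "the mean value of 6MWD in the control group was 297.9 and the standard deviation was 37.4". The SD of the change is not given, so I assume 20, 37.4, 50 and 60 m.
- Gain in CG: not given, assumed 0.
- Patients per arm: 33, since all randomised participants are to be analysed with multiple imputation.

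**The plan's own figure.** The plan gives no expected AUC. Its sample size reproduces without one. A one-way four-group F test with means 297.9, 332.4, 329.9 and 335.9, SD 37.4, alpha 0.0083 and power 0.80 gives 26 per group. Then 26/0.8 = 32.5, rounded up to 33, and 4 × 33 = 132. The ROC analysis plays no part in it.

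**Literal reading: marker X = gain, state Y = 1 if X ≥ 54**

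1. AUC = P(X of a responder > X of a non-responder) + ½ P(tie). Every responder has X ≥ 54 and every non-responder has X < 54, so AUC = 1.
2. The DeLong variance is the variance of the responders' placement values divided by their number, plus the same term for non-responders. Every placement value is 1, so both terms are 0.
3. The test of two arms is z = (1 − 1)/√(0 + 0) = 0/0, which is undefined.
4. A simulation (3,000 replicates per arm, n = 33) agreed: AUC was 1.000 at minimum and maximum, with DeLong variance 0, in all three arms at all four SDs. This confirms an identity and does not depend on the SD.

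The true responder shares do differ. Share = 1 − Φ((54 − mean gain)/SD). For PQG at SD 37.4, (54 − 34.5)/37.4 = 0.521, giving 30.1%.

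| SD of change (assumed) | PQG | AG | PAG | CG |
|---|---|---|---|---|
| 20 m | 16.5% | 13.6% | 21.2% | 0.3% |
| 37.4 m | 30.1% | 27.8% | 33.4% | 7.4% |
| 50 m | 34.8% | 33.0% | 37.4% | 14.0% |
| 60 m | 37.3% | 35.7% | 39.5% | 18.4% |

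**Alternative 1: marker = arm versus CG, state = responder**

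1. For a binary marker, AUC = 0.5 + ½ (sensitivity + specificity − 1).
2. With equal arms and responder shares p1 (intervention) and p0 (CG), sensitivity = p1/(p1 + p0) and specificity = (1 − p0)/((1 − p0) + (1 − p1)).
3. PQG at SD 37.4: sensitivity = 0.301/0.375 = 0.803; specificity = 0.926/1.625 = 0.570; AUC = (0.803 + 0.570)/2 = 0.686. AG gives 0.675 and PAG 0.700.
4. Substituting and simplifying, with S = p1 + p0: AUC = 0.5 + (p1 − p0)/(2 S (2 − S)). This is the risk difference, rescaled by a factor that depends on the overall responder share.
5. The rescaling can mislead. For PQG, going from SD 20 to SD 37.4 raises the risk difference from about 16 to about 23 points (16.5 − 0.3; 30.1 − 7.4), while the AUC falls from 0.762 to 0.686.

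**Alternative 2: marker = gain, state = arm versus CG**

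AUC = Φ(mean gain/(SD√2)), which gives 0.743, 0.727 and 0.764 for PQG, AG and PAG at SD 37.4. This is not degenerate, but it makes no use of the 54 m definition that the paragraph sets out.

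Under either alternative the three curves would share the CG patients but have different treated patients. Neither the plain paired nor the plain independent form of the DeLong test fits that structure.

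**The case against.** The best defence is that the text never calls 6MWD gain the marker. It calls it a classification criterion, and the next sentence supplies the cut-off. Together the two sentences may describe only the state, with the intervention as the implied marker, as the stated purpose suggests. On that reading the AUCs are not degenerate and, at 0.686, 0.675 and 0.700, they follow the same order as the responder shares.

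This stands in part: an AUC of 1 follows from the literal reading and not from every conceivable one. It does not rescue the paragraph. Arm versus control is not stated as the marker, and it conflicts with computing one AUC for each intervention group. Inside a group, arm membership is constant, and a constant marker gives an AUC of 0.5 through ties. The arm-versus-control version also adds nothing to the responder shares themselves.

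Two further objections hold. The analysis is supplementary, and the primary 6MWD question is addressed by the analyses in the preceding paragraph. Three AUCs of exactly 1 with no variance would also look odd to a careful analyst, so a claim that they would be published as perfect efficacy is speculation.

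A separate analysis plan might name a marker. The article itself, however, fixes the unit, variable, cut-off, test, software and significance level, and these do not work together.

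**Conclusion.** The concern holds in this form: only one patient-level variable is named, and read literally it is both marker and state. Each intervention arm's AUC is then 1 whenever both classes are present, and the DeLong test is undefined. That result is algebraic and rests on no assumed SD. The responder shares and the alternative AUCs do rest on the assumed SD of change, normal gains and zero gain in CG.

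Three stronger conclusions that a reader might draw are not supported:

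- **That every AUC must be 1 whatever the authors meant.** Two other readings give values between 0.5 and 1, though the text specifies neither.
- **That the AUCs would often be undefined for want of responders.** That would be common only in an arm with no gain, and no AUC is planned for CG. In the intervention arms, fewer than two patients in either class occurred in at most about 5% of simulated arms (AG at SD 20 m), and in 0.1% or fewer at SD 37.4 m and above.
- **That the primary result is at risk.** The continuous 6MWD comparison and the sample size do not use this analysis.

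The paragraph should be fixed because every reading of it needs a rewrite. It is a defect in a supplementary analysis and not a threat to the trial.

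**What to change.** Replace the ROC and DeLong paragraph with a supportive responder analysis, labelled secondary to the continuous 6MWD comparison:

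- Report the proportion with a 6MWD gain of at least 54 m in each of the four arms.
- Report the risk difference of each intervention arm versus CG, and of PAG versus PQG and versus AG, with score-type 95% confidence intervals.
- Use the multiply imputed data already planned, imputing the distance and then applying the 54 m cut.
- Treat any logistic model adjusted for baseline 6MWD as optional, and fit it with a penalty. CG may have few or no responders: with 33 patients, the chance of none is 0.926^33, about 8%, at a share of 7.4% (SD 37.4 m), and 0.985^33, about 60%, at 1.5% (SD 25 m). An ordinary fit would then separate.

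If the authors want to keep an ROC curve, they must name the marker, the state and the comparison group, and use a test suited to a shared control arm.

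The change is to wording only. It needs no new data, visits or participants.

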### Adverse events

All adverse events will be recorded in the case report form throughout the trial. Adverse events related to exercise and acupuncture (such as muscle and joint injuries, severe pain, local hematoma, infection, and abscess), including discomfort after treatment, will be promptly and in detail recorded. The assessor will collect from the patient a detailed description of the category and severity of the adverse event, and any correlation with the treatment. If an adverse event is serious and related to the trial, the patient will be withdrawn from the study and receive appropriate medical care.

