### Blinding

Blinding of subjects and interveners is not feasible due to the inclusion of exercise and acupuncture interventions in this study. However, assessors will remain blinded. All participants and assessors will receive strict instructions not to discuss or disclose any information regarding the intervention methods prior to the start of assessments. Independent research personnel will be present at all times to ensure successful blinding procedures are maintained consistently throughout data collection processes. In cases where assessors become aware of a subject’s intervention method during assessment, their involvement will be terminated promptly with replacement by another assessor.

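### The Adverse events section has the assessor ask patients about treatment-related events, which conflicts with the assessor blinding set out in the Blinding section

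*Protocol article*

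**What the plan says.** The Blinding section of the protocol article accepts that participants and treating staff know the allocation: "Blinding of subjects and interveners is not feasible due to the inclusion of exercise and acupuncture interventions in this study". It continues: "However, assessors will remain blinded". Three measures support this. Participants and assessors receive "strict instructions not to discuss or disclose any information regarding the intervention methods prior to the start of assessments". Independent personnel attend data collection. If an assessor learns the intervention during an assessment, "their involvement will be terminated promptly with replacement by another assessor".

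The Adverse events section sets the safety procedure. On timing: "All adverse events will be recorded in the case report form throughout the trial"; events related to exercise and acupuncture are also to be noted promptly. The examples given are "such as muscle and joint injuries, severe pain, local hematoma, infection, and abscess", and discomfort following treatment is included. On who does it: "The assessor will collect from the patient a detailed description of the category and severity of the adverse event", "and any correlation with the treatment".

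The article uses the word assessor in both sections and defines no separate safety assessor.

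**The concern.** The two sections give the assessor incompatible instructions. One forbids hearing about the intervention before assessments start. The other requires a conversation with the patient about whether an event was connected with the treatment. It is hard to hold that conversation without learning that there was needling or Qigong training.

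Assessor blinding carries much of the weight here because patients and interveners are unblinded. The primary outcome is a walk at the patient's fastest pace (Primary outcome section). Respiratory muscle pressures and isokinetic strength also call for maximal effort (Secondary outcomes section). Instruction and encouragement from the tester can influence such tests, and a blinded tester is the only masking at that point. Any loss of blinding would fall mainly on the treated arms, since control participants have no sessions that could cause needling or Qigong events.

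**Working it through.** No calculation decides this point. The check is to set the sections side by side.

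1. **Who.** The Blinding section masks assessors; the Adverse events section gives the interview to the assessor. With one term and no second role defined, the natural reading is that they are the same staff. The article does not say so outright.

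2. **What is learned.** The interview covers the type of event, its severity and its relation to treatment. A needle-site haematoma or abscess points to the acupuncture or combined arm; an exercise injury points to the Qigong or combined arm. Such an event can therefore reveal treated versus control status. It need not separate a single-treatment arm from the combined arm.

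3. **When.** Table 1 places the outcome tests at week 0 and week 8. Adverse events are recorded throughout the trial, and treatment-related ones promptly. Events in the 8 treatment weeks would thus normally be recorded before the week-8 tests. The sentence about the assessor's interview gives no time of its own, so exposure before week 8 is the likely reading but is not fixed by the text.

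4. **Whether the safeguards cover it.** The ban on disclosure is contradicted by the interview's own content. The replacement rule is tied to awareness gained during an assessment and does not clearly reach an interview held between visits. If it is read to cover such interviews, carrying out the Adverse events section would itself trigger replacement.

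5. **Which outcomes.** Those at stake are the effort-dependent tests run by an assessor: walk distance, inspiratory and expiratory pressures, and isokinetic strength. The Hamilton anxiety and depression scales are completed by the unblinded patients, so assessor blinding does not protect them in either case.

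**The case against.** The strongest reply is that the article does not identify the person taking adverse events as the outcome rater, and that a condensed article may leave delegation of tasks to the full protocol. The interview might also come after the week-8 tests, where it could not affect them. Both are possible, but the article does assign the task to the assessor, and prompt recording suggests earlier contact. The two sections need reconciling whichever was intended.

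Some limits do stand. Only participants with an event are affected. Muscle pain or a haematoma could arise in any arm, from maximal strength testing or from the blood draw. Independent personnel attend data collection, and an assessor who becomes aware of the intervention during assessment is replaced.

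Two stronger readings are tempting. A reader might infer that the trial's only protection against bias is broken. The documents do not support that: allocation is randomized, the analyst is blinded, and the statistician takes no part in outcome measurement. A reader might also infer a bias as large as the planned differences between the combined and single arms, which are 38 − 34.5 = 3.5 and 38 − 32 = 6 (Sample size calculation section). No figure in the documents supports this. An arm's mean shifts by the lift per affected participant times the share affected. If, purely as an assumption, the lift were 5 to 10 m and the share 10 to 20%, the shift would be 5 × 0.10 = 0.5 m to 10 × 0.20 = 2 m. That is about 1 to 6% of the planned 34.5 (0.5/34.5 and 2/34.5) and below both planned differences. In addition, many of these events would not tell a single arm from the combined arm.

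**Conclusion.** The conflict is real and should be resolved. As written, the plan can show the blinded assessor which event-reporting participants are in a treated arm before the week-8 effort-dependent tests, and the replacement rule does not clearly deal with this. The conclusion assumes that the same staff are meant in both sections and that at least some interviews take place before week 8; both are the natural reading, but neither is stated. The size of any bias cannot be estimated from the documents, because they give neither an expected event rate nor the effect of an unblinded tester. The point does not undermine the randomization, the sample size or the analysis.

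**What to change.** Reword the Adverse events section so that existing unblinded study staff who do not measure outcomes collect adverse events and their relation to treatment. Use the same questions, schedule and mode of contact in all four arms. The weekly telephone call described in the Control group section could serve if it is made to every arm. Add that outcome assessors neither see adverse-event records nor ask about treatment until the week-8 assessments are complete.

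Equal contact matters. Weekly calls are described only for the control group, and treatment sessions exist only in the other three. Leaving event collection to interveners in the treated arms and to callers in the control arm would ascertain events unequally, even with identical questions.

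The cost is a wording change, a reassigned task and added call time in the three treated arms. Sample size, outcome visits and analysis are unaffected.
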